## 14. OBJECTIVES

The ultimate aim of this project is to answer the question whether insufficient EN should or should not be supplemented with PN early in the disease course of critical illness in children.

The scientific objectives of the study are divided into 3 main work-packages (WP 1-3) and are the following:

- WP1: Performing and completing the first well-designed and sufficiently powered, multicentre RCT to test the effects of early PN supplementation on the health of critically ill children. The short-term outcome analysis, as well as a substantial part of the long-term follow-up, will be completed within the time frame of the study.
- WP2: an economic evaluation, in which costs and cost-effectiveness will be investigated of early versus late PN supplementation during hospitalization.
- WP3: Starting to unravel potential mechanisms that underlie any difference in acute and long term outcome with early or late PN supplementation by studying metabolic, endocrine, inflammatory and (epi.)genetic markers in the blood of critically ill children included in the study.

### Primary Objective:

The primary focus of the PEPaNIC study is clinical outcome, more specifically the acquisition of new ICU infections, the dependency on intensive medical care and convalescence from critical illness, this is part of WP1.

The primary efficacy endpoints for this RCT are the incidence of new infections and the time to discharge alive from ICU. We expect to see a decrease in secondary infections from 20% to 15%, which is based on a previous study in critically ill children in Leuven (12) and on retrospective data in critically ill children who were admitted for at least four days in the PICU, Rotterdam.

Number of patients with new infections and types of infection will be assessed by numbers and percentages, and the duration of any antibiotics therapy initiated after randomisation for those patients requiring antibiotics will be analysed by non-parametrical tests. As the time of ICU discharge to the regular ward may be affected by the availability of beds on the regular wards, which could induce bias, we a priori decided to analyse “time to discharge from ICU” as “time to ready for discharge from ICU”. A patient is considered “ready for discharge” as soon as all clinical conditions for ICU discharge have been fulfilled (no longer in need for vital organ support). Time to discharge alive from ICU will be reported by Kaplan-Meier plots, with ICU non-survivors censored beyond the longest ICU stay of survivors and censoring time of patients still in the ICU at closing of the data file (90 days after last patient inclusion) over both treatment groups. The impact of “late PN” versus “early PN” will be analysed, with and without correction for age, nutritional status and risk categories and type and severity of illness, by Cox proportional hazard analysis. The distribution of the actual time to discharge from ICU will be reported for ICU-survivors and ICU-non-survivors separately. In view of the time window of the randomised intervention in ICU, also the proportion of patients staying beyond 8 days in ICU will be reported. Analyses on blood and urine for the primary clinical analyses include routine chemistry, haematology, and markers of inflammation. Further epigenetic, metabolic, endocrine and inflammatory measurements on stored samples in the context of mechanistic analyses will be

planned. All new infections of the lungs, the blood stream, the urinary tract and wounds are recorded by an infectious disease specialist. A nosocomial infection is defined as a localized or systemic condition 1) that results from adverse reaction to the presence of an infectious agent(s) or its toxin(s) and 2) that was not present or incubating at the time of admission to the PICU. The information used to determine the presence and classification of an infection should be a combination of clinical findings and results of laboratory and other tests. Definitions various types of proven and suspected infections will be used according to clinical, laboratory evidence and/or supportive data. WHO definitions for nosocomial infections will be used (13).

**TABLE I. Simplified criteria for surveillance of nosocomial infections**

| Type of nosocomial infection | Simplified criteria                                                                                                                                                                                                                                   |
|-------------------------------------|--------------------------------------------------------------------------------------------------------------------------------------------------------------------------------------------------------------------------------------------------------------|
| Surgical site infection             | Any purulent discharge, abscess, or spreading cellulitis at the surgical site during the month after the operation                                                                                                                                           |
| Urinary infection                   | Positive urine culture (1 or 2 species) with at least $10^5$ bacteria/ml, with or without clinical symptoms                                                                                                                                                  |
| Respiratory infection               | Respiratory symptoms with at least two of the following signs appearing during hospitalization: 
 
— cough
 
— purulent sputum
 
— new infiltrate on chest radiograph consistent with infection
 
 |
| Vascular catheter infection         | Inflammation, lymphangitis or purulent discharge at the insertion site of the catheter                                                                                                                                                                       |
| Septicaemia                         | Fever or rigours and at least one positive blood culture                                                                                                                                                                                                     |

*WHO definitions for nosocomial infections (13).*

Clinical evidence is derived from direct observation of the infection site or review of other pertinent sources of data, such as the patient's chart. Laboratory evidence includes results of cultures, antigen or antibody detection tests, or microscopic visualization. Supportive data are derived from other diagnostic studies, such as x-ray, ultrasound, computed tomography (CT) scan, magnetic resonance imaging (MRI), radiolabel scan, endoscopic procedure, biopsy, or needle aspiration. It will be recorded during the entire ICU period until discharge, death or until day 90 of admittance.

Bacteraemia is further classified by responsible pathogen and as catheter-related blood stream infection versus other bacteraemia.

To study the underlying physiological mechanisms of enteral nutrition (EN) intolerance of critically ill children and to identify markers of tolerance for EN to use in future intervention studies clinical signs of intolerance (gastric residual volume, diarrhoea, vomiting, abdominal swelling) will be recorded. Buccal swabs will be collected at several moments and will be stored for analysis (epithelial cell expression of chemokines).

#### Secondary Objectives:

WP2. Performing an economic evaluation study, investigating the effects of early versus late PN supplementation during hospitalization.

WP3. Starting to unravel potential mechanisms that underlie any difference in acute and long-term outcome with early or late PN supplementation by studying metabolic, endocrine, inflammatory and (epi.)genetic markers in the blood of critically ill children included in the study.

### **STUDY DESIGN**

This study is a large, three-centre, non-blinded, randomized, controlled study. The study intervention will last for a maximum of 7 days per patient, and the entire study (final patient completed study) is anticipated to last 4 years, excluding the long-term follow-up, the health-economic analysis and the completion of the mechanistic studies. (See figure)

Consecutive patients are randomly assigned to one of the two treatment study groups using a digital system with central, computerised randomisation. Randomisation – in a one to one allocation ratio - is performed per centre and using permuted blocks of 10 per diagnostic stratum. The block size remains unknown to bed-side physicians and nurses, responsible for patient recruitment and therapy assignment.

The “early PN” strategy will be the nutritional management currently applied in the participating centres, acting as “control”.

The “late PN” strategy comprises initiation of this strategy only after day 7 in PICU.

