## **15. STUDY POPULATION**

### **15.1 Population Base**

The patient group of critically ill children (0 – 18 yrs), represents a significant proportion of the ICU population. In 2010, the 10-bed Leuven PICU admitted 527 critically ill children, the majority requiring artificial ventilation. 61% of the cases were admissions after cardiac surgery. Individual critically ill children had a median ICU stay of 3 days (inter-quartile range of 2-6 days) (mean 5.5 days). In the 35-bed PICU of the University of Rotterdam 1700 critically ill children were admitted in 2010 of which 600 (35.3%) were ventilated. Patients stayed in the PICU for a median of 2 days (mean 7.8 days). We anticipate an inclusion rate of 200-250 patients per centre per year.

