### **15.2 Inclusion criteria**

All critically ill children admitted to the participating PICUs are evaluated for nutritional risk and eligibility for inclusion in this study. All critically ill children, with nutritional risk score (STRONGkids® see appendix) 2 or more, who are not able to take oral nutrition and are expected to stay in PICU for more than 24h are eligible for inclusion.

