## **18.2 Randomisation, blinding and treatment allocation**

### ***Randomization***

The study will use a prospective, randomized, controlled, parallel-group design. On admission patients will be randomly assigned to receive EN combined with early PN or only EN. At ICU admission, consecutive patients will be randomly assigned to one of these two treatment groups using a centralized computer randomisation. Randomisation will be done in a 1:1 allocation ratio in permuted blocks of 10 (The block size remains unknown to bed-side physicians and nurses, responsible for patient recruitment and therapy assignment) and stratified according to primary diagnostic category on admission:

I Medical-ICU admissions (infectious or non-infectious): (a) respiratory (b) cardiac (c) renal (d) haematological/oncological (e) gastro-intestinal/hepatic (f) neurological (g) other.

II Surgical-ICU admissions (elective or urgent) according to referral discipline (a) cardiac surgery (b) solid organ transplants (c) pulmonary/oesophageal surgery (d) abdominal surgery (e) neurosurgery (f) trauma/orthopaedic surgery (g) burns (more than 20% BSA is burned and/or patient requires ventilation)

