### ***Blinding of treatment allocation***

Treating physicians and patients cannot be blinded. All outcome assessors, which are investigators not directly involved in the patients care (such as statisticians, laboratory personnel, infectious disease specialists, pathologists and physiotherapists involved in the strength measurement) as well as physicians and nurses in the conventional wards are blinded to treatment allocation.

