### **21.2 Recruitment and consent**

The study protocol and consent forms will be sent for approval by the Institutional Review Board of the Katholieke Universiteit Leuven and the Erasmus MC (Lokale uitvoerbaarheid) and by the competent Belgian and Dutch authorities (CCMO). Written informed consent is obtained from the parents or the legal guardian by the investigator's team or one of the supervising doctors, who will inform the parents of the patients (and the patients themselves if the age is > 12 years) and ask for their consent. The parents / legal guardians and (if applicable) the patients will receive a patient information letter and an informed consent form.

Written informed consent will be obtained from the patient or the closest family member or legal guardian. For planned PICU admissions after elective procedures, informed consent will be asked beforehand, if possible.

For emergency PICU admissions, treatment allocation will be done after assessment of the patient for eligibility by the attending physician within the time frame of two hours. If eligible, the patient will be randomized into the study and the allocated glucose infusion (with micronutrients) will be started. Informed consent will be asked within the time frame of 24 hours (deferred informed consent) as a nutritional regimen has to be initiated already on admission. When consent is given, the allocated nutritional regimen will proceed (Early (with additional lipids and protein targeting nutritional goals < day3) vs Late (no PN)). When NO consent is given, the nutritional regimen and glucose infusion will be placed under responsibility of the supervising clinical team of doctors.

The parents or legal guardians can withdraw the patient from the study at any time, without penalty or impact on treatment.

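### The protocol relies on hiding one fixed block size of 10, yet prints it; if recruiting staff learn it, at most one assignment in six is known in advance in this open-label trial

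*Supplement*

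**What the plan says.** All references are to the final protocol.

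- **Allocation.** The Study Design section says that randomisation, "in a one to one allocation ratio", "is performed per centre and using permuted blocks of 10 per diagnostic stratum". The Summary says the same. Section 18.2 (Randomization) repeats it: "Randomisation will be done in a 1:1 allocation ratio in permuted blocks of 10". It lists seven medical and seven surgical diagnostic categories. No other block size is mentioned.
- **Concealment of the size.** In all three places the protocol adds: "The block size remains unknown to bed-side physicians and nurses, responsible for patient recruitment and therapy assignment". It does not say how the size is kept from these staff. The promise does not name the other people who take consent.
- **Open treatment.** Section 18.2 (Blinding): "Treating physicians and patients cannot be blinded".
- **Who decides on entry.** For emergency admissions, "treatment allocation will be done after assessment of the patient for eligibility by the attending physician" (section 21.2). Consent is taken by the investigator's team or a supervising doctor.
- **Judged criteria.** Section 15.2 admits children "expected to stay in PICU for more than 24h are eligible for inclusion". Section 15.3 excludes those expected to die within 12 hours.
- **Safeguards.** Allocation is central and computerised, for consecutive patients (Study Design). All admitted children are assessed for eligibility (15.2), and a register of everyone evaluated is kept (18.6). Screening and inclusion are followed daily (19.2). Outcome assessors, including infectious disease specialists, are blinded (18.2). Outcomes are analysed with and without correction for risk factors (20.1, 20.3).

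The SAP covers a later secondary analysis and does not deal with allocation.

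**The concern.** A central system hides the next assignment, but it cannot stop someone inferring it from earlier assignments that are visible on the unit. With a single known block size, once five children in a block have gone to one arm, every remaining child in that block goes to the other. The sequence therefore depends on keeping one number secret, and the protocol publishes that number beside the promise of secrecy.

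If a clinician with a preference for or against early feeding could foresee the arm, the judged criteria leave some room to enrol or hold back a particular child. The arms could then differ in case mix, which matters for both primary endpoints: new infections and time to discharge alive. The opportunity is most practical in large strata that fill quickly. Cardiac surgery in Leuven is the likely example, since "61% of the cases were admissions after cardiac surgery" there in 2010.

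**Working it through.** The plan gives no figure for predictability, so there is none to reproduce.

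**Inputs from the protocol:** block size 10, five per arm; 14 categories x 3 centres = 42 cells; 1440 children.

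**1. Certain assignments.** There are C(10,5) = 252 equally likely blocks. An assignment is certain when one arm has already been used five times. The number of blocks in which this holds, by position:

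| Position | Blocks | Share |
|---|---|---|
| 1-5 | 0 | 0% |
| 6 | 2 | 0.8% |
| 7 | 12 | 4.8% |
| 8 | 42 | 16.7% |
| 9 | 112 | 44.4% |
| 10 | 252 | 100% |

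Sum: (2 + 12 + 42 + 112 + 252)/252 = 420/252 = 1.667 per block, or **16.7%**. The closed form 2m/(m+1) with m = 5 gives the same. The ceiling is 1440/6 = 240 assignments.

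**2. Unfinished blocks.** With equal cells of 34 or 35 children, each cell has three complete blocks (3 x 1.667 = 5 certain assignments) and a remainder of four or five children with none. That gives 42 x 5 = 210, and 210/1440 = **14.6%**. Uneven cells (assumed distributions) give 14.8% to 15.5%.

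**3. Predictable with at least 75% certainty.** Add the states in which one arm has been used four times and the other 0, 1 or 2 times (certainty 5/6, 4/5 and 3/4). They occur in 6, 25 and 60 of 252 blocks for each arm, so 2 x (6 + 25 + 60)/252 = 0.722 per block. The total is 1.667 + 0.722 = 2.389 per block, or **23.9%**.

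**4. Best guess.** Always guessing the arm that is behind is right **65.3%** of the time. This needs no knowledge of the block size, because the running count in a stratum returns to balance at the end of every block. Hiding the size therefore protects only in part even if it succeeds.

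**5. Random block sizes.** These come from simulation, with sizes equally likely and an observer who knows the list of sizes and every earlier assignment in the stratum.

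| Sizes | Certain | At least 75% | Best guess |
|---|---|---|---|
| Fixed 10 | 16.7% | 23.9% | 65.3% |
| Even, 10 to 20 | 0.2-0.3% | about 9% | 63% |
| 4, 6, 8 | 2.3% | about 34% | 68% |

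The gain is in certainty; ordinary guessing hardly changes. Smaller blocks make guessing easier than the present design.

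**6. Illustration of bias (assumption, not derivable from the documents).** Suppose the true infection risk of enrolled children differs by d between moments when late PN and early PN are predicted, and that all recruiters act on every guess in the same direction. The spurious difference is (2 x 0.653 - 1) x d = 0.306d. With even sizes 10 to 20 it is (2 x 0.629 - 1) x d = 0.258d. The standard error of the risk difference is sqrt(2 x 0.175 x 0.825/720) = 2.0 points.

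| d (points) | Bias, fixed 10 | Two-sided false-positive rate | Bias, sizes 10-20 |
|---|---|---|---|
| 2 | 0.6 | 6% | 0.5 |
| 3 | 0.9 | 7% | 0.8 |
| 5 | 1.5 | 12% | 1.3 |
| 8 | 2.5 | 23% | 2.1 |

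If staff acted only on certain assignments, d = 5 would give 0.167 x 5 = 0.8 points and a false-positive rate of 7%.

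**The case against.** A block of 10 is already large, and the protocol does more than hide its size. Allocation is central and for consecutive patients, with a two-hour window for emergency admissions. Every evaluated child is registered, a CONSORT diagram is planned, and screening is followed daily, so selective enrolment would be hard to practise and could leave a trace. Outcome assessors are blinded. Adjustment covers type and severity of illness, age, nutritional status and risk scores, which is much of the case mix that steering would disturb. All of this stands, and it limits the risk. It does not remove it: adjustment reaches only measured factors, and the register does not prevent prediction.

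A reader might go further and infer that recruiters work from the printed protocol, so that one assignment in six is in fact known and both primary endpoints are biased. The documents do not support that. No section says that bedside staff read the protocol, or that all earlier assignments in a stratum are seen and counted. PN in the control arm depends on enteral intake, so the feeding a child receives is an imperfect sign of the arm. The gap d is an assumption, and nothing has been calculated for time to discharge.

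It is also fair that random block sizes change best guessing little. Their benefit is the near-removal of certain assignments.

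**Conclusion.** The point holds as an avoidable weakness in concealment, not as evidence of bias. The protocol depends on the secrecy of one fixed number that it prints three times, with open treatment and partly judged eligibility, and it gives no means of withholding that number. If staff learn the size and track their stratum, at most 16.7% of assignments (about 15% with unfinished blocks) are certain before enrolment, and 23.9% can be predicted with at least 75% certainty in completed blocks. These are ceilings that rest on both conditions. The bias in section 6 of the working is an illustration over an assumed range. Whether any bias arises, and how large, cannot be settled from the documents.

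**What to change.** In the existing central system, draw the size of each new block at random from sizes no smaller than 10 (for example even sizes 10 to 20) in every centre-by-diagnosis stratum. Delete the block size from the Summary, the Study Design section and section 18.2, and hold it in a restricted randomisation document. Do not mix in smaller blocks.

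The cost is a system setting and three wording changes, with no extra patients. The downside is a slightly larger possible imbalance in unfinished blocks within a stratum.

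A rule that forces an assignment only at a set imbalance is an option for reducing guessing further, but is not needed here. Nor is a separate lock on category and eligibility, since a central stratified system that allocates after eligibility assessment largely implies it.

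This is a design-stage change. The SAP in the same supplement describes all 1440 children as already randomised, so it cannot alter that sequence.

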#### Timeline of the entire study

##### *Work package 1 (WP1)*

The first milestone (M1) of the study will be the start of the large RCT in the centre of the coordinating investigator/project leader in Leuven, closely followed by our center at Erasmus MC-Sophia. The study will continue in parallel in all three centers until patient number 720 will have left the ICU. At that time point, a safety interim analysis will be performed (milestone M2). Three possible scenarios are foreseen depending on the result of this analysis:

1. The interim analysis shows harm by “Late PN” and the clinical study will be prematurely stopped (“no go” decision).
2. The data safety monitoring board requests a new safety interim analysis because of reasonable doubt about the safety of “Late PN”. In that case, the study will continue in all three centers under very strict monitoring, and planning of additional safety interim analyses if necessary, until the end of the study (either when completed or when prematurely stopped).
3. The study will be continued in all three centers as planned, without further interim analyses, until all 1440 patients have been included.

In all three scenarios the end of the study will be milestone 3 (M3). Together with the finalization and cross-check of the clinical database and the writing of the corresponding manuscript of the short-term clinical outcome, this will constitute deliverable 1 (D1). Hence, D1 is guaranteed irrespective of premature interruption of the study. In view of the outcome results of the adult EPaNIC study, such premature interruption will rather be unlikely. The applicants have extensive experience in the management of large RCTs, including in critically ill children, and handling and monitoring of the corresponding large clinical databases. This invaluable experience will be key to successful accomplishment of this ambitious study.

